# A Patient Registry for the Management of Uterine Fibroids in Canada: Protocol for a Multicenter, Prospective, Noninterventional Study

**DOI:** 10.2196/10926

**Published:** 2018-11-20

**Keywords:** Canada, leiomyoma, registries

## Abstract

**Background:**

Uterine fibroids are the most common benign tumor in women. Among those with fibroids, approximately 30% become symptomatic, with abnormal uterine bleeding, pelvic pain, and bulk symptoms. Despite the high prevalence of fibroids, little information is available regarding symptoms, treatment choices, and outcomes for patients.

**Objective:**

A Canada-wide patient registry was established to understand the real-world practice. This registry included patient presentation and treatment preferences, health care provider attitudes, and clinical outcomes in the management of symptomatic uterine fibroids.

**Methods:**

This study is a prospective, noninterventional, observational patient registry. It will include women diagnosed with uterine fibroids and being managed for symptoms. Participant inclusion criteria were (1) at least 18 years of age, (2) premenopausal with a confirmed diagnosis of uterine fibroids, and associated symptoms, and (3) initiating treatment (drug intervention, procedure intervention, or a combination of both) or watchful waiting. Patients (or legal representative) must understand the nature of the project and provide written informed consent before enrollment. Participant exclusion criteria were (1) they have known or suspected clinically significant pelvic pathology not associated with uterine fibroids, and (2) they are undergoing an emergency hysterectomy at the initial visit. Outcomes will be evaluated in the context of routine clinical practice.

**Results:**

Participant recruitment of this registry began in July 2015. This study currently has a total sample of 1500 patients.

**Conclusions:**

This registry, a first in Canada, will accumulate evidence on the risks and benefits of watchful waiting, and medical and procedural interventions. It will contribute to enhancing access to treatment options for patients.

**Trial Registration:**

ClinicalTrials.gov NCT02580578; https://clinicaltrials.gov/ct2/show/NCT02580578 (Archived by WebCite at http://www.webcitation.org/6yax4Hpvr)

**International Registered Report Identifier (IRRID):**

RR1-10.2196/10926

## Introduction

Uterine fibroids (UF) are benign, monoclonal, hormone-sensitive, smooth muscle tumors that represent the most common solid pelvic tumor in women [1-3]. They affect 20% to 40% of women during their reproductive years [4]. Despite their prevalence, very little is known about the etiology of the disease, burden of illness, and quality of life associated with the condition. Although most patients with UF are asymptomatic, UF can cause heavy and prolonged menstrual bleeding, pelvic pressure or pain, bulk symptoms, and reproductive dysfunction. Patients with UF show increased use of analgesics, sanitary products, and health care resources. There are more physician visits, increased absenteeism, and a decline in energy, and overall activities, including sexual activity [5]. Apart from epidemiologic data, the natural history of UF is poorly understood.

In addition to the palpation of an enlarged irregular uterine contour on pelvic examination, ultrasonography is used to confirm the diagnosis of UF [6]. Recently magnetic resonance imaging (MRI) has gained popularity, but the cost and access to this technology prohibit routine screening. In a uterus with fewer than 5 lesions, ultrasonography appears to be equally effective as detection by MRI and virtually identical for assessing their size and location [7]. However, when the number of lesions is higher, MRI exceeds the technical limitations of ultrasound in precise fibroid mapping and characterization.

A significant issue in the field of fibroid identification is the necessity for differentiating fibroids from other pathologies such as adenomyomas and uterine neoplasms. Although uncommon in women less than 40 years old [8], these conditions require the differential diagnosis with fibroids because the treatment options and prognosis may differ [9]. Patterns of use and accuracy of diagnostic imaging of UF have not been studied systematically in the publicly funded Canadian health care system.

Treatment options for UF patients should ideally address 3 goals: (1) relief of signs and symptoms, (2) sustained reduction in fibroid size, and (3) retention or enhancement of fertility if desired. At the same time, treatment should also aim to improve quality of life, minimize side effects, be convenient for patients, and target UF directly [10]. Medical, procedural, or combined treatment options are available for patients with symptomatic UF. However, there were no medications to treat these women in Canada until 2013 when ulipristal acetate (UPA) was approved.

UPA has shown to be more effective than placebo [11] and as effective as the injectable gonadotropin-releasing hormone agonist leuprolide acetate [12] for treating UF symptoms. Leuprolide acetate received Health Canada indication for preoperative improvement of anemia in symptomatic UF women in 2017 [13]. The uptake, long-term clinical and patient-reported outcomes, efficacy, safety, as well as the pharmacoeconomics of indicated and off-label treatment options for these patients in Canada, have yet to be determined.

In the past 15 years, there has been only 1 completed registry for patients with UF who have undergone uterine artery embolization [14]. In the United States, the COMPARE-UF trial is underway [15]. A Canadian prospective patient registry provides the opportunity to address many unanswered questions, particularly the management patterns and outcomes associated with different treatments for UF and patients’ preferences for, and satisfaction with, managing UF symptoms.

With this background in mind, the objectives of this study are to (1) enhance the understanding of the natural history of symptomatic UF, (2) understand Canadian provider and patient preferences for managing symptomatic UF, (3) examine factors that have an impact on the uptake of UF treatment options and compliance with therapy, (4) examine the effectiveness and efficiency of UF treatment options across ethnicities in real-world practice in Canada, and (5) provide real-world data characterizing long-term clinical and patient-reported outcomes, including effectiveness and safety, associated with different UF management options.

## Methods

### Overall Study Design and Plan

The CAnadian women wiTh Uterine fibroids REgistry (CAPTURE) is a prospective, observational cohort study (NCT02580578) that will include women who have been diagnosed with symptomatic UF. Outcomes will be evaluated as part of routine clinical practice. The target study population will include patients with a diagnosis of UF from 20 study sites across Canada. Participating physicians will not be required to perform any medical procedure that is outside their normal clinical practice. Serious and nonserious adverse drug reactions (ADRs) will be followed up as per local standard of care and as expected in an observational research study. Similarly, both serious and nonserious adverse events (AEs) during and following procedural intervention will be reported. Each study site was responsible for local ethics review board approval as per their institutional policy.

### Participants

Approximately 1000 patients will be enrolled from 20 Canadian investigational sites, including both academic and community practices. Inclusion criteria for the study are premenopausal women at least 18 years of age with confirmed diagnosis and symptoms associated with UF that are being observed (watchful waiting), currently being treated, or initiating treatment (drug intervention, procedure intervention, or a combination of both). All patients (and the patient’s authorized legal representative) should understand the nature of the project and provide written informed consent before or at the initial study visit. Exclusion criteria for the study are known or suspected significant pelvic pathology not associated with UF and patients undergoing an emergency hysterectomy at the initial visit.

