### Baseline Visit

The baseline visit will involve (1) obtaining informed consent, (2) checking for inclusion/exclusion criteria, (3) collecting demographic information, (4) obtaining a medical history, and (5) assessing patient current health status. This will be followed by patient assessments that involve questions on UFs using the EuroQol 5-Dimensions 5-Levels (EQ-5D-5L) survey, the Uterine Fibroid Symptom and Quality of Life (UFS-QOL) questionnaire, the Aberdeen Menorrhagia Severity Scale (AMSS) questionnaire, and evaluation for concomitant medications and history of previous procedural interventions.

The EQ-5D-5L [16] is a validated 5-question survey with a visual analog scale used to measure health outcomes that provides a simple descriptive profile and a single index value for health status. The UFS-QOL [17] is a validated 37-question disease-specific symptom and health-related quality of life questionnaire for UF. It has been used extensively in studies to assess the impact of the disease in patients and treatment options in randomized clinical trials. The AMSS questionnaire is a validated 15-question survey that evaluates the severity and effect of bleeding that occurs during and between menses. There are 7 baseline questions for UF patients asking about the purpose of their visit and what outcome they are hoping to achieve.

If deemed eligible for registry participation, the patient will return for a visit in 3 to 6 months. When available, imaging and other test results (biopsies, blood work) will also be documented.

**Table 1 table1:** Schedule of events of the CAPTURE study at baseline and scheduled visits.

Examinations	Scheduled follow-up visits			
	Baseline	3- to 6-month^a^	12-month^a^	24-month^a^
Signed informed consent form^b^	✓	—	—	—
Inclusion/exclusion criteria	✓	—	—	—
Demographics	✓	—	—	—
Medical history	✓	—	—	—
Fertility wishes	✓	✓	✓	✓
Blood work (hemoglobin)^c^	✓	✓	✓	✓
Gynecologic symptoms	✓	✓	✓	✓
Ultrasound of fibroids	✓	✓	✓	✓
Type and location of fibroids	✓	—	—	—
Endometrial biopsy^c^	✓	—	—	—
Planned/updated management plan	✓	✓	✓	✓
UFS-QOL^d^	✓	✓	✓	✓
Bleeding assessment^e^	✓	✓	✓	✓
EQ-5D-5L^f^	✓	✓	✓	✓
Concomitant medications	✓	✓	✓	✓
Adverse events	—	✓	✓	✓

^a^Visits can be performed by telephone or in clinic; however, an in-person visit is preferred.

^b^Must be obtained from patient prior to study enrollment.

^c^To be captured if available.

^d^UFS-QOL: Uterine Fibroid Symptom and Quality of Life questionnaire.

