### Visits at Three to Six Months, Twelve Months, and Twenty-Four Months

These visits can be performed in the clinic or via telephone; however, an in-person visit is preferred. Participants will be evaluated for updates and an assessment of the management plan, and for ADRs (if medication was prescribed at the previous visit). Also, patient questionnaires (EQ-5D-5L, UFS-QOL, and AMSS) will be administered. Follow up will occur after the baseline meeting at 3 to 6 months, 12 months, and 24 months.

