### Statistical Methods

The analysis will include all patients enrolled in the study who have been entered into the database.

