### Statistical Analysis

The goal of this study is to establish a registry of Canadian patients with symptomatic UF. We have recruited a sample of 1500 patients to help describe the management of UF in this population.

Initially, exploratory data analysis will summarize all variables of interest by reporting means and standard deviations for continuous variables, and frequencies (percentages) for categorical variables. Analysis of variance will be used to compare continuous variables between treatment groups of interest. Chi-square tests will be used to compare categorical variables between the 2 groups. A linear mixed model will be employed to examine the association between treatment groups while adjusting for other covariates of clinical interest. These variables include demographics, UF history, comorbidities, medications, and medical tests (both current and previous).

The model will include a time-by-treatment-interaction term to determine whether treatments have improved quality of life relative to other treatment groups. Furthermore, a random effect will be included at the patient level to incorporate correlation arising from the repeated measures design of the study.

Since this is an observational registry, missing data and drop-outs (ie, early study termination) are expected. Statistical techniques will be used to examine the missing data (including logistic regression) and, if feasible, multiple imputations will be used to make any adjustments.

Additionally, where imputation techniques are not adequate, sensitivity analysis will be employed. All parameter estimates, confidence intervals, and *P* values will be reported from the model, and a 2-sided significance level of .05 will be used.

The original terms used by participating physicians to identify ADRs will be coded using the Medical Dictionary for Regulatory Activities (MedDRA). The MedDRA system organ class and preferred term will be used to present the number and percentage of patients with ADRs, the drug relationship, seriousness, and intensity of ADRs. Chi-square tests will be employed to compare the number of ADRs between groups of interest.

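### Abstract and Methods disagree on whether women already on treatment are eligible, and pooling them with initiators biases the planned quality-of-life comparison

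*Protocol article*

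**What the plan says.** The article gives eligibility twice. The abstract's third inclusion criterion covers women "initiating treatment (drug intervention, procedure intervention, or a combination of both) or watchful waiting". The Participants section covers women "being observed (watchful waiting), currently being treated, or initiating treatment", which adds a class that the abstract does not have.

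The analysis set is not narrowed. Statistical Methods states: "The analysis will include all patients enrolled in the study who have been entered into the database". The section on the scheduled visits sets the clock: "Follow up will occur after the baseline meeting at 3 to 6 months, 12 months, and 24 months". Statistical Analysis names a linear mixed model with a patient-level random effect and says: "The model will include a time-by-treatment-interaction term to determine whether treatments have improved quality of life relative to other treatment groups". Its covariates include fibroid history and medications, both current and past.

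The Baseline Visit section provides for "evaluation for concomitant medications and history of previous procedural interventions". Among the objectives in the Introduction, the fourth is to "examine the effectiveness and efficiency of UF treatment options across ethnicities in real-world practice in Canada", and the fifth concerns long-term outcomes, including effectiveness and safety, under different management options.

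**The concern.** A reader of the abstract would take this for a cohort of women starting a management option or being observed. Under the Methods it also contains women whose treatment began before enrolment, and nothing in the article separates them in the comparative model.

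For a woman who starts treatment at the baseline visit, the later trajectory contains the response to treatment, subject to the usual confounding. For a woman already on treatment, two things differ. Part or all of the response may lie before her first questionnaire, so it cannot appear in her trajectory. She also belongs to a selected group, because women who stopped early for lack of response or intolerance are less likely to be found among current users. If treatment groups contain different shares of such women, the interaction reflects that mix as well as the treatments. The conclusions at stake are those on effectiveness (objectives 4 and 5).

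**Working it through.** **No figure to reproduce.** The article gives no power calculation, effect size or share of already-treated women, so the check compares the text and then works under stated assumptions.

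**Step 1, text side by side.** Abstract: initiating or watchful waiting. Participants: watchful waiting, current treatment or initiating. Analysis set: everyone enrolled and entered. Clock for the scheduled visits: the baseline visit. Judgement of benefit: time-by-treatment interaction. Already-treated women therefore enter the model unless some rule that the article does not state removes them.

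**Step 2, expected contrast.** Assumed quantities:
- delta: true effect of a treatment against a comparator that contains no already-treated women
- f: share of the treatment group already treated at baseline
- g: fraction of delta already reached by baseline in those women

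Initiators contribute delta to the contrast, and already-treated women contribute delta x (1 - g). The mixture is

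(1 - f) x delta + f x delta x (1 - g) = delta x (1 - f x g).

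The proportion lost is f x g:

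| f | g = 0.5 | g = 1 |
|---|---|---|
| 0.10 | 5% | 10% |
| 0.25 | 12.5% | 25% |
| 0.50 | 25% | 50% |

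**Step 3, simulation.** With 200,000 women per group, one baseline and one follow-up measurement, delta = 10 and g = 1, the simulated contrast was 9.98 at f = 0, 7.47 at f = 0.25 and 5.07 at f = 0.50. The formula gives 10, 7.5 and 5.

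**Step 4, does covariate adjustment help?** Adding a main-effect indicator for being already treated at baseline left the three simulated values unchanged. That is expected: the indicator is constant over time within a woman, so it moves her level and not her slope. Only a term that lets the trajectory differ by prior treatment, or a restriction of the sample, changes the interaction.

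**Step 5, two active groups.** If both groups contain already-treated women, the contrast is delta1 x (1 - f1 x g1) - delta2 x (1 - f2 x g2). Take two equally effective options with delta = 10 and g = 1. With f1 = 0.25 and f2 = 0, the expected contrast is 7.5 - 10 = -2.5 where the truth is 0. The error can therefore favour either side, depending on which group has more women already treated.

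The formula covers only the effect absorbed into baseline. It contains nothing for the selective loss of early stoppers, which may act in another direction.

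**The case against.** The strongest reply is that the article leaves much of the model open. It does not define change from baseline, does not say whether treatment group is fixed or updated, and does not forbid separating initiators. Such details usually sit in an analysis plan, which is not shown. Much of the registry is also descriptive: already-treated women are useful for natural history, preferences and uptake. The Potential Limitations section acknowledges selection bias and confounding, and current and past medications are listed as covariates.

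Part of this stands, and it limits several stronger readings:
- A reader might infer that a woman operated on at, say, month 9 has her earlier visits counted as procedure time. That needs a fixed label, which the article does not state. The article also schedules pre- and postoperative questionnaires, and a visit one year after hysterectomy that replaces the remaining scheduled visits.
- A reader might infer that only drug groups are affected. The text does not support this: earlier procedures are recorded at baseline, and women may have been under observation before enrolment.
- A reader might infer a definite large loss of effect. Both f and g are unknown, and a full plateau (g = 1) is an extreme assumption for women who must have symptoms to be eligible.

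What does not fall away is the stated text. The eligibility conflict is on the page, the analysis set is stated without restriction, and the listed covariates, entered as main effects, do not correct the interaction. A general remark on selection bias does not identify this source of it.

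**Conclusion.** The eligibility statements contradict each other and must be reconciled. As the analysis is described, pooling already-treated women with initiators biases the time-by-treatment contrast that is meant to show quality-of-life benefit, and main-effect adjustment for medications leaves that bias in place.

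The size cannot be derived from the article. Under the simple model, with g between 0.5 and 1 and an unaffected comparator, the loss is 12.5-25% at f = 0.25 and 25-50% at f = 0.50, before any selection effect. Between two active groups, the direction depends on which has more already-treated women. Enrolling these women is no error for the descriptive objectives; the problem is confined to the comparative use of their data under objectives 4 and 5. It is best treated as a cheap improvement. The article does not support the view that the registry's comparisons are invalid as a whole.

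**What to change.** 1. Make the eligibility wording identical in the abstract and the Participants section, stating the criteria that were actually applied. Recruitment has ended, so this is a correction of the record.
2. Use the baseline concomitant medications and previous procedures to classify each woman as already treated, initiating or in watchful waiting, with the rule written down before analysis.
3. Fit the comparative effectiveness model in initiators and watchful-waiting patients. Count time from treatment start where that date is recorded, and use the preoperative questionnaire as baseline for procedures.
4. Report already-treated women separately and descriptively, and keep them in the analyses of management patterns and preferences. Report their number by group, which would replace the assumed f.
5. Treat time-updated treatment status as an optional sensitivity analysis only. Worsening symptoms may prompt a switch, so updating the status brings in time-dependent confounding.

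The cost is analysis wording, derivation work and a smaller comparative sample. The article does not say that drug start dates, or dates of the decision to observe, are captured. It also lists no questionnaires at unscheduled visits, so a treatment begun between scheduled visits may have no questionnaire close to its start. Where the date is missing, the plan should say how the woman is handled.

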### Withdrawal of Participants

Participation in this registry is voluntary, and patients may withdraw at any time and for any reason. Once the patient informs the site staff that she wishes to withdraw her participation, a “Withdrawal from registry” form will be completed with the date and reason. The patient will be informed that all data collected up to that point will be used in the analysis. From that point on, the patient will no longer be contacted for the registry, and no further data on that participant will be collected.

### Participants Lost to Follow Up

Efforts will be made to keep patients in the registry for at least 24 months. A patient will be considered to have missed a study visit after all efforts have been made by site personnel to contact the patient to reschedule within 1 month of the missed appointment. If a patient has missed a follow-up visit, all efforts should be made to reach the patient to ensure that subsequent follow-up visits are completed.

### Study Visits

The visit schedule is comprised of 4 study visits (baseline, 3- to 6-month, 12-month, and 24-month; Table 1) and pre-, intra-, and postoperative visits for patients undergoing procedural interventions (Table 2).

### Baseline Visit

The baseline visit will involve (1) obtaining informed consent, (2) checking for inclusion/exclusion criteria, (3) collecting demographic information, (4) obtaining a medical history, and (5) assessing patient current health status. This will be followed by patient assessments that involve questions on UFs using the EuroQol 5-Dimensions 5-Levels (EQ-5D-5L) survey, the Uterine Fibroid Symptom and Quality of Life (UFS-QOL) questionnaire, the Aberdeen Menorrhagia Severity Scale (AMSS) questionnaire, and evaluation for concomitant medications and history of previous procedural interventions.

The EQ-5D-5L [16] is a validated 5-question survey with a visual analog scale used to measure health outcomes that provides a simple descriptive profile and a single index value for health status. The UFS-QOL [17] is a validated 37-question disease-specific symptom and health-related quality of life questionnaire for UF. It has been used extensively in studies to assess the impact of the disease in patients and treatment options in randomized clinical trials. The AMSS questionnaire is a validated 15-question survey that evaluates the severity and effect of bleeding that occurs during and between menses. There are 7 baseline questions for UF patients asking about the purpose of their visit and what outcome they are hoping to achieve.

If deemed eligible for registry participation, the patient will return for a visit in 3 to 6 months. When available, imaging and other test results (biopsies, blood work) will also be documented.

**Table 1 table1:** Schedule of events of the CAPTURE study at baseline and scheduled visits.

Examinations	Scheduled follow-up visits			
	Baseline	3- to 6-month^a^	12-month^a^	24-month^a^
Signed informed consent form^b^	✓	—	—	—
Inclusion/exclusion criteria	✓	—	—	—
Demographics	✓	—	—	—
Medical history	✓	—	—	—
Fertility wishes	✓	✓	✓	✓
Blood work (hemoglobin)^c^	✓	✓	✓	✓
Gynecologic symptoms	✓	✓	✓	✓
Ultrasound of fibroids	✓	✓	✓	✓
Type and location of fibroids	✓	—	—	—
Endometrial biopsy^c^	✓	—	—	—
Planned/updated management plan	✓	✓	✓	✓
UFS-QOL^d^	✓	✓	✓	✓
Bleeding assessment^e^	✓	✓	✓	✓
EQ-5D-5L^f^	✓	✓	✓	✓
Concomitant medications	✓	✓	✓	✓
Adverse events	—	✓	✓	✓

^a^Visits can be performed by telephone or in clinic; however, an in-person visit is preferred.

^b^Must be obtained from patient prior to study enrollment.

^c^To be captured if available.

^d^UFS-QOL: Uterine Fibroid Symptom and Quality of Life questionnaire.

^e^Tool for assessment is the Aberdeen Menorrhagia Severity Scale questionnaire.

^f^EQ-5D-5L: EuroQol 5-dimensions 5-levels survey used to measure health status.

**Table 2 table2:** Schedule of events of the CAPTURE study at procedural intervention and hysterectomy.

Examinations	Procedural intervention^a^			Hysterectomy
	Preoperative	Intraoperative	Postoperative	1-year follow up
Signed informed consent form	—	—	—	—
Inclusion/exclusion criteria	—	—	—	—
Demographics	—	—	—	—
Medical history	—	—	—	—
Fertility wishes	—	—	—	—
Blood work (hemoglobin)^b^	✓	—	—	—
Gynecologic symptoms	—	—	—	✓
Ultrasound of fibroids	✓	—	—	—
Type and location of fibroids	—	—	—	—
Endometrial biopsy	—	—	✓	—
Planned/updated management plan	✓	—	—	—
UFS-QOL^c^	✓	—	✓	✓
Bleeding assessment^d^	✓	—	✓	—
EQ-5D-5L^e^	✓	—	✓	✓
Concomitant medications	✓	—	—	—
Adverse event	✓	✓	✓	—

^a^Procedural intervention is not mandatory in the registry, and data will be collected if physician and patient decide on a procedural intervention to address symptoms associated with uterine fibroids.

^b^To be captured if available.

^c^UFS-QOL: Uterine Fibroid Symptom and Quality of Life questionnaire.

^d^Not required if patient undergoes hysterectomy procedure. Otherwise the tool for assessment is the Aberdeen Menorrhagia Severity Scale questionnaire.

^e^EQ-5D-5L: EuroQol 5-dimensions 5-levels survey used to measure health status.

